## INTRODUCTION

1

Heart failure (HF) with preserved ejection fraction (HFpEF) is a heterogeneous syndrome that is the predominant form of HF in western countries.^1^, ^2^, ^3^, ^4^ Chronotropic incompetence (ChI), defined as the inability to increase heart rate during exercise adequately, is commonly present (ranging from 20 to 75%) in HFpEF patients.^5^, ^6^, ^7^, ^8^, ^9^, ^10^, ^11^ Furthermore, ChI has been proposed as a pathophysiologic mechanism associated with poorer outcomes and decreased functional capacity in a subgroup of patients with HFpEF.^8^, ^12^, ^13^

Data from current registries show a high proportion (ranging from 50% to 80%) of beta‐blockers prescription in HFpEF patients regardless of the heart rhythm.^3^, ^14^ Nevertheless, there is no well‐established evidence endorsing the effect of beta‐blockers. For instance, recent studies suggested that patients with an ejection fraction of 50% or greater did not see any benefits from receiving beta‐blockers.^15^, ^16^, ^17^ Even more, the evidence is missing stratifying patients with HFpEF across ChI status.

When ChI is present, beta‐blockers may have negative effects on functional capacity and other surrogates of the disease severity by exacerbating the ChI. Thus, we hypothesize that deprescribing beta‐blockers in this particular scenario will translate into an improvement in short‐term maximal functional capacity. The purpose of this randomized controlled study is to evaluate the short‐term effects of beta‐blockers withdrawal on the functional capacity, cognitive function, and quality of life (QoL) in patients with HFpEF and documented ChI.

The primary endpoint of the study is absolute and relative changes in peak oxygen uptake (peakVO2) at 15‐day after the intervention. The secondary endpoints are: (a) 15‐day absolute changes in cognitive function assessed by the Mini‐Mental State Examination (MMSE) and Montreal Cognitive Assessment (MoCa); (b) 15‐day absolute changes in echocardiogram parameters (E/E' ratio and left atrial volume index); (c) 15 days absolute changes in QoL assessed by Minnesota Living With Heart Failure Questionnaire (MLHF); and (d) 15 days absolute and relative changes in prognostic biomarkers (N‐terminal pro‐B‐type natriuretic peptide ‐NT‐proBNP‐ and serum carbohydrate antigen 125‐CA125‐).

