### Statistical plan

2.6

Continuous variables will be presented as mean ± SD or median (interquartile range—IQR) as appropriately; categorical variables as percentages. All statistical comparisons will be made under the intention‐to‐treat principle. A repeated‐measures analysis of variance (ANOVA) will be used for the comparisons of continuous outcomes among the two‐intervention groups. The interaction group*time‐points will be tested to unveil any effect of time (15 and 30 days) on the magnitude of the intervention. Only in the event of imbalance in baseline characteristics, repeated‐measures analysis of covariance (ANCOVA) will be used. A two‐sided *P*‐value of <0.05 will be considered to be statistically significant for all analyses. All analyses will be performed with Stata 14.1.

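### The 0.05 significance rule covers every analysis, so seven secondary measures (nine tests) can each yield a significant result with no gate on the primary and no exploratory label

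*Protocol article*

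**What the plan says.** The decision rule is in section 2.6 (Statistical plan): "A two‐sided *P*‐value of <0.05 will be considered to be statistically significant for all analyses". The same section names one method for all continuous endpoints: "A repeated‐measures analysis of variance (ANOVA) will be used for the comparisons of continuous outcomes among the two‐intervention groups".

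The endpoints are in the Introduction (section 1). The primary is peakVO2: "The primary endpoint of the study is absolute and relative changes in peak oxygen uptake (peakVO2) at 15‐day after the intervention". Four groups of secondary endpoints follow it there, all at 15 days:

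- Group (a), cognition, is measured on two scales, MMSE and MoCa, each as absolute change.
- Group (b), echocardiography, has two indices, E/E' and left atrial volume index, each as absolute change.
- Group (c), quality of life, has one score, the MLHF, as absolute change.
- Group (d) takes two blood markers, NT-proBNP and CA125, on both scales of change: "15 days absolute and relative changes in prognostic biomarkers".

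The purpose statement in the Introduction sets cognition and quality of life next to functional capacity: the trial is to "evaluate the short‐term effects of beta‐blockers withdrawal on the functional capacity, cognitive function, and quality of life (QoL"). The null hypothesis and the sample size in section 2.5 concern peakVO2 alone. The article gives no testing order for the secondary endpoints, no division of alpha, no condition that the primary succeed first, and no statement that they are exploratory.

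**The concern.** The article does more than stay silent on multiplicity. It fixes a threshold and extends it to everything. Followed literally, any one of the secondary results may be called statistically significant at P<0.05, whatever happens to peakVO2 and however many other secondary results are null.

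What is at stake is how secondary findings are reported. A trial with a null peakVO2 result could still report a significant change in cognition, quality of life, an echocardiographic index or a biomarker. Nothing in the stated rule would mark that result as weaker evidence than the primary. Because the purpose statement treats cognition and quality of life as effects under evaluation, a reader could give such a result more weight than it deserves.

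**Working it through.** **Reference figure.** The article states no family-wise error rate for the secondary endpoints, so there is none to reproduce. The inputs are the per-test level and the number of tests.

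**Inputs.**

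- Per-test level: two-sided 0.05 (section 2.6).
- Number of tests (Introduction):

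| Group | Measures | Scales of change | Tests |
|---|---|---|---|
| (a) cognition | MMSE, MoCa | absolute | 2 |
| (b) echocardiography | E/E', left atrial volume index | absolute | 2 |
| (c) quality of life | MLHF | absolute | 1 |
| (d) biomarkers | NT-proBNP, CA125 | absolute and relative | 4 |
| Total | 7 measures | | 9 tests |

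Seven tests is the count if each biomarker is tested on one scale only. The two versions of the primary endpoint are outside this family.

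- Correlation between test statistics: not given. It is an assumption, varied below.

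**Step 1: independent tests, no true effect on any secondary measure.** The chance of at least one P<0.05 is 1 − 0.95^m.

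- m = 7: 1 − 0.95^7 = 1 − 0.698 = 0.302.
- m = 9: 1 − 0.95^9 = 1 − 0.630 = 0.370.

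**Step 2: correlated tests.** Take m standard normal statistics with a common correlation r and reject if any |Z| exceeds 1.96. The values below were simulated with 1,000,000 draws per setting and agree with direct numerical integration.

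| Common correlation r | 7 tests | 9 tests |
|---|---|---|
| 0 | 0.30 | 0.37 |
| 0.3 | 0.27 | 0.33 |
| 0.5 | 0.23 | 0.27 |
| 0.7 | 0.18 | 0.20 |
| 0.8 | 0.15 | 0.17 |

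**Step 3: a less uniform pattern.** A common correlation between, say, MoCa and left atrial volume index is artificial. Suppose instead that only the natural pairs are strongly correlated (MMSE with MoCa; E/E' with left atrial volume index; for nine tests, also the absolute and relative versions of each biomarker). With 0.5 to 0.9 within pairs and 0 to 0.2 elsewhere, seven tests give about 25% to 29% and nine tests about 28% to 35%. Both ranges lie inside the span of Step 2.

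**Step 4: ratio to the nominal level.** The smallest value is 0.15/0.05 = 3 times, and the largest is 0.37/0.05 = 7.4 times.

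**The case against.** The strongest reply is that this is a journal article. Ordering, gating and labelling of secondary endpoints commonly sit in the full protocol or SAP, neither of which is shown. A sentence setting the two-sided level could coexist with a hierarchy there, since fixed-sequence testing also uses 0.05 at each step. The article already separates primary from secondary endpoints and powers only peakVO2, and nominal P-values for secondary endpoints are common in a trial of 52 patients.

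Much of this stands. The absence of a multiplicity scheme alone would not be a finding, and the primary analysis is not harmed. What remains is the sentence itself. It attaches the term statistically significant to every analysis without qualification, so an unseen hierarchy would have to restrict it.

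A reader might infer three stronger things that the article does not support:

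- **That a false secondary claim is likely, or has a fixed 27% chance.** Every figure is below one half, applies only if no secondary effect exists, and depends on a correlation that the article does not give. The 27% belongs to nine tests at an assumed correlation of 0.5.
- **That success on either cognitive scale would count as success on cognition.** Section 2.4.3 says only that overall scores are analysed. It gives no either-or rule.
- **That the sponsor intends to rest a case for withdrawal on a lone secondary result.** No section says so. The wording merely does not prevent it.

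**Conclusion.** The point holds as a modest one about secondary claims. As written, section 2.6 lets any of seven secondary measures, in nine tests, be called significant at 0.05 regardless of the primary result. With no true secondary effect, the chance of at least one such result is about 15% to 37%, at least three times the nominal 5% throughout the range examined.

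That range rests on three assumptions: no effect on any secondary measure, normal test statistics, and a common correlation between 0 and 0.8. The counts of seven and nine come directly from the Introduction. If some secondary effects are real, the figures do not describe the trial's actual risk, but the rule still does not separate supportive from confirmed results. The conclusion on peakVO2 does not depend on this point.

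**What to change.** In section 2.6, remove the extension of the 0.05 rule to all analyses and replace it with text to this effect: *Statistical significance at the two-sided 0.05 level will be claimed for the primary peakVO2 test only. Secondary endpoints are supportive/exploratory and will be reported as estimates with 95% confidence intervals; any P-values for them are nominal and unadjusted for multiplicity.*

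If the sponsor wants a confirmatory secondary claim, a short fixed sequence can be pre-specified, tested only after a significant primary result, with all remaining secondary endpoints labelled exploratory. Which endpoints enter it and in what order is the sponsor's choice. If the full protocol or SAP already contains such a scheme, it is enough to make this sentence agree with it.

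The cost is two or three sentences, with no extra patients or data. The downside is that an isolated secondary P<0.05 cannot be reported as a confirmed effect.

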## RESULTS: CURRENT STATUS

3

The ethics committee approved the protocol of our center, following the principles of the Declaration of Helsinki and national regulations. The protocol is registered at EudraCT (2017‐005077‐39) and http://clinicaltrials.gov (NCT03871803). Patients started enrolling in October 2018. As of January 14th, 2020, a total of 28 were enrolled. We expect to finish the inclusion at the end of July 2020.

The median (IQR) age of patients included is 74.3 (68‐77) years, 19 (67.9%) are women, and 28 (100%) were previously admitted for acute heart failure. Median (IQR) of NT‐proBNP is 922 (397‐2016) pg/mL.

## DISCUSSION

4

### Background and rationale

4.1

HFpEF is a complex and heterogeneous clinical syndrome characterized by exercise intolerance, markedly reduced functional capacity,^28^, ^29^ normal left ventricular ejection fraction (>50%), and evidence of diastolic dysfunction and left atrial enlargement.^18^ Despite being a contemporary challenge, the pathophysiological mechanisms of impaired exercise capacity and poor quality of life in these patients are not yet entirely clarified.^30^, ^31^ Among cardiac mechanisms, ChI has been proposed as a pathophysiologic mechanism associated with poorer exercise capacity in a subgroup of patients with HFpEF.^6^, ^7^, ^8^ Along this same line, recent evidence has shown that ChI is frequently present (ranging from 20% to 75%) in HFpEF patients.^5^, ^6^, ^7^, ^8^, ^9^, ^10^, ^11^

From epidemiological perspective, patients with HFpEF are usually older, predominantly females and with high prevalence of other cardiovascular comorbid conditions such as atrial fibrillation, hypertension, and renal dysfunction^1^, ^2^, ^3^, ^4^ which in the end contribute to reduced exercise tolerance, and may explain the high proportion (ranging from 50% to 60%) of beta‐blockers prescription in HFpEF patients.^3^, ^4^, ^14^ Nevertheless, emerging evidence suggests that pharmacological heart rate lowering is not beneficial in patients with preserved ejection fraction.^15^, ^16^, ^17^ In this regard, the proposed pathophysiological mechanism of pharmacological heart rate lowering in HFpEF patients is the prolongation of the filling of the cardiac chambers, which increases filling pressures, left ventricular diastolic wall stress and central arterial pressures.^12^

To date, there is no convincing evidence to support the beneficial effects of beta‐blockers prescription in HFpEF patients.^32^, ^33^, ^34^, ^35^, ^36^ A recent meta‐analysis suggests a clinically beneficial effect of beta‐blockers in patients with HF and left ventricular ejection fraction ≥40%; however, the evidence to those with left ventricular ejection fraction >50% is limited.^37^ Recently, a recent secondary study from TOPCAT showed that for patients with an EF of 50% or greater, beta‐blocker use was associated with an increased risk of HF hospitalizations but not CVD mortality.^15^ However, no prior randomized clinical trial has explored the effects of beta‐blocker withdrawal on functional capacity in HFpEF patients with documented ChI.

### Biological plausibility

4.2

Currently, no study has evaluated the acute hemodynamic effects of beta‐blockers in HFpEF.^17^ However, clinical experience with these agents provides some insights. In this sense, some authors have suggested that prolonged diastolic filling related to heart rate lowering increases ventricular pressures in HFpEF patients.^17^, ^38^ Interestingly, beta‐blocker cessation would translate into a reduction in end‐diastolic pressures, as has been recently suggested with a decrease in natriuretic peptides following beta‐blockers withdrawal.^38^

Another potential beneficial effects of beta‐blockers withdrawal on HFpEF patients with ChI stand out: (a) increase in heart rate response during exercise which may be considered as a compensatory mechanism for maintaining cardiac output in patients with significant diastolic dysfunction; and (b) amelioration of delayed memory retrieval in cognitively impaired patients,^39^ and (c) attenuation arterial central pressures at rest and during exercise.^12^

### Feasibility and future implications

4.3

HFpEF is a heterogeneous syndrome in which no pharmacological therapy has shown promising results. Identifying those HFpEF patients with ChI could help us to characterize the different phenotypes of this syndrome and optimize medical treatment. In this regard, beta‐blockers withdrawal could represent a treatment option in those patients with documented ChI. This strategy is an attempt to move forward into precision medicine in HFpEF by identifying the ChI phenotype and treating it accordingly.

## CONCLUSION

5

To date, there is no evidence about the benefit of beta‐blockers in HFpEF patients, even less in those with documented ChI. In this randomized controlled trial, we aim to evaluate the effects of beta‐blocker withdrawal on short‐term functional capacity in stable HFpEF patients.

